## Abstract

**Abstract:**

**Introduction:**

Some cancers are diagnosed late, making them harder to treat. People with an undiagnosed cancer may use over-the-counter medications to manage non-specific cancer-related symptoms that often mimic other more common, easily treatable conditions. Results from the original Cancer Loyalty Card Study (CLOCS) suggest there may be an increase in purchases of pain and indigestion medication 8–9 months before an ovarian cancer diagnosis. We aim to validate the CLOCS findings by exploring whether a significant change in medication purchases could be an indication for early signs of the following cancer types: oesophageal, stomach (gastric), colorectal (bowel), pancreatic, liver, bladder, endometrial, uterine sarcoma, ovarian and vulval, using data collected through store loyalty cards.

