While advances in cancer care have been significant, the patient factors associated with earlier presentation to healthcare when individuals are experiencing symptoms are less understood.^11^ The Model of Pathway to Treatment stipulates that an individual’s symptom appraisal involves the evaluation of new symptoms, which is influenced by psychological, social and cultural factors, and may be through self-medication, symptom monitoring and changes in behaviour.^13^ Historically, research on these behaviours has been largely qualitative;^11^ however, more recent studies have begun exploring interventions to promote earlier help-seeking.^14^,^16^

In 2023, the findings from the Cancer Loyalty Card Study (CLOCS) offered a novel observational case-control study approach to test whether purchasing patterns captured through loyalty cards (store reward cards that record customers’ purchase histories) could provide early warning signals of ovarian cancer.^17^ The results showed that, compared with participants without ovarian cancer, those with ovarian cancer had a significant increase in purchases of indigestion and pain medications up to 9 months before a diagnosis of ovarian cancer was received (OR 1.38, 95% CI 1.04 to 1.83, p=0.03).^17^

Ovarian cancer was chosen to be the first type of cancer to be explored due to its non-specific symptoms and patient-reported experiences using the over-the-counter medication. Building on the findings of the original CLOCS, CLOCS-2 aims to validate these findings across ovarian cancer as well as nine additional cancers: oesophageal, stomach (gastric), colorectal (bowel), pancreatic, liver, bladder, endometrial, uterine sarcoma, ovarian and vulval cancers. These cancer types have been identified as cancers in which patients experience non-specific symptoms and self-care for^11^ and with highest gains in patient treatment outcomes and survival if diagnosed early.

A phased approach will be used. Four cancers (oesophageal, colorectal (bowel), pancreatic and ovarian), for which symptom profiles and patient pathways are better characterised, will be prioritised for full evaluation. The remaining six cancers will initially be piloted, as there is greater uncertainty regarding symptom presentation and the feasibility of recruitment within these groups. The pilot phase will inform the feasibility of wider inclusion of these cancers in the study.

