### Sample size and statistical power

A power calculation was conducted for the following four cancers: ovarian, pancreatic, oesophageal and colorectal. This calculation was based on the former CLOCS study^19^ which was conducted using conditional logistic regression of matched pairs. The calculation assumes an effect size of OR=1.38, with 80% power at alpha=0.05 and estimates n=223 case-control pairs are needed for each cancer type. To allow for attrition of ~10%, the total number we will aim to recruit for each of these four cancers will be 250 (n=1000). No power calculation has been done for the remaining six types of cancer as these are being piloted, but the aim is to recruit 75 participants per cancer.

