### Statistical methods

We will use descriptive statistics to provide details on the characteristics of cases and controls by sociodemographic (eg, age, sex and ethnicity), cancer type and by risk factors.^11^ We will report feasibility factors, including the number of participants with a loyalty card from either participating retailer, the number with cards from both retailers and the number of years of data available for analysis.

We will aim to define the time by which cases and controls become statistically significantly different in their purchase behaviours using a multivariable, conditional logistic regression model with cancer as the outcome and ‘purchase proportion’ at different timepoints to diagnosis as the exposure, adjusting for potentially confounding variables. This analysis will be repeated and stratified by cancer type, stage at diagnosis and sociodemographic factors. Analyses will be performed for different types of medications and cancers separately and combined.

We will compare proportions using Fisher’s exact tests comparing target (items suspected to be used to treat cancer symptoms) and non-target (all other items) purchases. These comparisons will be made between cases and controls at each month prior to diagnosis. For controls, the reference will be the average monthly proportions of purchases across the observation period. Target items for analysis will include, but will not be limited to, medications for pain, indigestion, bloating relief and fatigue, along with other items commonly used to alleviate cancer-related and non-specific symptoms.^11^

We will conduct exploratory analyses to establish a potential risk profile for each participant and cancer type. This will be defined as a mathematical summation of all relevant risk factors, based on the published literature.^11^ In line with the findings from the original CLOCS, this analysis will be exploratory.^19^ Furthermore, we will investigate additional methods that leverage autocorrelation in the longitudinal data. Specifically, we will examine the evolution of individual purchasing frequencies and purchase trajectories to identify patterns—such as increases in purchases prior to diagnosis or distinct purchase peaks—that may be indicative or predictive of disease onset and time to onset.

All analyses will be done using statistical software R.

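### The study sets out to validate a specific CLOCS result, but its primary objective and analysis are an open search in which no test is designated as the replication

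*Protocol article*

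**What the plan says.** **Aim.** The Abstract states: "We aim to validate the CLOCS findings by exploring whether a significant change in medication purchases could be an indication for early signs", and goes on to list ten cancers. The Introduction repeats it: "CLOCS-2 aims to validate these findings across ovarian cancer as well as nine additional cancers".

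**Finding to be validated.** The Abstract describes it as "there may be an increase in purchases of pain and indigestion medication 8–9 months before an ovarian cancer diagnosis". The Introduction gives the estimate, "OR 1.38, 95% CI 1.04 to 1.83, p=0.03", but describes the rise as extending up to 9 months before diagnosis.

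**Sample size.** Under Sample size and statistical power: "The calculation assumes an effect size of OR=1.38, with 80% power at alpha=0.05", giving 223 pairs for each of ovarian, pancreatic, oesophageal and colorectal cancer. The other six cancers are piloted at 75 each without a power calculation.

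**Primary objective.** Study objectives asks at which time points, over 6 years, purchasing differs significantly between cases and controls. It covers all ten cancers, and both symptom-management items and other items.

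**Analysis.** Statistical methods fits conditional logistic regression at several time points, repeated by cancer, stage and sociodemographic factors. It adds: "Analyses will be performed for different types of medications and cancers separately and combined". The item list is open: "Target items for analysis will include, but will not be limited to, medications for pain, indigestion, bloating relief and fatigue". The risk-profile work is labelled exploratory, as is the interim analysis in its own section. The main regression and the monthly Fisher tests carry no label, whether primary, confirmatory, replication or exploratory.

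**The concern.** A validation claim needs the earlier hypothesis carried forward as a named test: same exposure, same disease, a fixed window, one model, one alpha. The article uses the earlier odds ratio for its sample size but does not carry the hypothesis into the objective or the analysis. If pain and indigestion purchases before ovarian cancer show nothing, while a different product class in a different cancer is significant, the text gives no agreed reading of that pattern.

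This is separate from the search over months. It remains even if a single window is fixed, because the choice of medicine class and cancer is still open. The Introduction foresees individual alerts or public messages about purchase thresholds, so a mistaken claim of validation could have consequences beyond the paper.

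**Working it through.** **1. The plan's own figures.**
- Attrition: 223 / 0.9 = 247.8, so 248; the article rounds to 250.
- Total cases: 4 × 250 + 6 × 75 = 1450, which agrees.
- Original result: SE = ln(1.83/1.04) / (2 × 1.96) = 0.144; z = ln(1.38)/0.144 = 0.322/0.144 = 2.23; two-sided p = 0.025, consistent with the stated 0.03.
- The 223 pairs cannot be confirmed, because the exposure scale and distribution are not given. For a continuous exposure with the OR per SD and no within-pair correlation, pairs = 2 × (1.960 + 0.842)² / 0.322² = 151.3, so 152. Dividing by (1 − ρ) gives 223 at ρ of about 0.32, a value the article does not state. The point here does not depend on this, so 223 pairs and 80% power are taken as given.

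**2. What would define a replication test, and what the text fixes.**

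| Element | Fixed? |
|---|---|
| Cancer | Partly: ovarian is one of four powered cancers |
| Model | Partly: matched conditional logistic regression |
| Alpha | 0.05, in the power calculation only; sidedness not stated |
| Medicine class | No: classes separately and combined, open list |
| Window | No: 8–9 months in the Abstract, up to 9 months in the Introduction |
| Criterion for success | No |

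**3. Chance of at least one positive, one fixed window, no true effect, each test two-sided at 0.05.** Cancers have different case-control pairs and are taken as independent.
- One medicine class, four powered cancers: 1 − 0.95⁴ = 0.185.
- Four named classes (pain, indigestion, bloating, fatigue) tested separately in four cancers: let q be the chance that at least one of four equally correlated z-tests is significant within a cancer; the rate over four cancers is 1 − (1 − q)⁴.

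| Assumed correlation between classes | q | Over four cancers |
|---|---|---|
| 0 | 0.185 | 0.560 |
| 0.5 | 0.156 | 0.492 |
| 0.8 | 0.114 | 0.384 |

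The q values come from numerical integration over the shared component; simulation gives the same rates to within a percentage point. One named test has a rate of 0.05, or 0.025 in the direction of the CLOCS result.

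**4. Power cost of adjusting the extension tests.** 80% power at two-sided 0.05 implies an expected z of 1.960 + 0.842 = 2.802. With Holm over three cancers, the first step is at 0.05/3 = 0.0167, critical value 2.394. Power = Φ(2.802 − 2.394) = Φ(0.408) = 0.66. Restoring 80% at that step needs 223 × ((2.394 + 0.842)/2.802)² = 297.4, so 298 pairs.

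**The case against.** **Multiplicity belongs in the SAP.** Ordering of tests and alpha splitting are commonly left to a SAP, and this is a condensed article. That stands for the method of adjustment, whose absence is not the point. Which hypothesis the study exists to confirm is set by the objectives, and the stated primary objective is an open search while the stated aim and power basis are validation. That mismatch is in the text. A SAP that narrowed it would depart from the published objective.

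**The aim is wider than ovarian cancer.** Correct: the Introduction extends validation to nine further cancers, so analysing all ten follows the stated aim. The wider aim still does not say which test confirms the CLOCS result.

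**There is already a hierarchy.** Partly correct. Four cancers are prioritised and powered, six are piloted, and the power calculation applies to each of the four rather than to a single contrast. This ranks cancers. It does not choose a medicine class or window.

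**Any result at p<0.05 could be called validation.** A reader might infer this, but the document does not say it. The 0.05 appears only in the power calculation, and an ovarian estimate for these medicines falls within the planned analyses. What can be said is that no rule is given.

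**Larger error rates.** Extending the four classes to all ten cancers gives 70% to 87%, up to 17 times 0.05. Those figures count six unpowered pilot cancers, and the top one also needs uncorrelated medicines, so they are not relied on. Separate cancers are also separate questions; the family-wise rate matters only where one positive among several would support a single claim.

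**Conclusion.** The point holds in a limited form. The article states a validation aim and powers four cancers on the original OR, but its objective and analysis do not designate a replication test or fix its medicine class and window. It does not follow that the authors would accept any significant result as validation.

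The size is 18.5% for one class over the four powered cancers, assuming only independence between cancers. It is about 38% to 56% if the four named classes are tested separately, at assumed correlations of 0.8 to 0. Treating those classes as four tests is itself an assumption, since the article names them as examples of target items. All figures assume one fixed window and leave out the months, the strata and any items added to the list.

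This should be corrected. It is a matter of stating the hypothesis and does not alter the design.

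**What to change.** Before the interim analysis at 6 months of recruitment, which includes an exploratory look at the data, amend Study objectives and Statistical methods as follows.

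1. Name one replication contrast: pain plus indigestion purchases combined, in ovarian cancer, by conditional logistic regression at two-sided 0.05, in a single window. Fix that window by reconciling the Abstract (8–9 months) with the Introduction (up to 9 months). State that this test decides whether the CLOCS result was replicated.
2. Report the same exposure and window in oesophageal, colorectal and pancreatic cancer as extension tests. If Holm adjustment is used across the three, state that power at the first step is about 66% rather than 80%.
3. Label other medicine classes, items added to the list, the six pilot cancers and the pooled analyses as exploratory, with estimates and confidence intervals and no claim of validation.

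**Cost.** Wording in the protocol and SAP. The ovarian test keeps the stated 223 pairs and 80% power. The price is that results outside the named contrasts can be reported only as hypothesis-generating, and that adjusted extension tests have less power unless recruitment rises to about 298 pairs per cancer.

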#### GP practices

After submitting an expression of interest, new RDNs or PCNs will receive further study information and set up an organisation information document (OID) for each participating GP practice. The OID developed with the North London RDN will serve as a template for other networks. A brief site initiation visit (SIV) will be held with each new RDN/PCN conducted by the CLOCS-2 team.

Clinical team members at each GP practice will identify potential study participants with a primary diagnosis of one of the eligible cancers, received in the last 2 years prior to recruitment date. Eligible cases will be randomly selected if the number of potential participants exceeds the required size. GP practices will match invited cases with eligible controls based on age bracket, sex and the number of inhabitants. Controls will be randomly sampled from participants without a cancer diagnosis who meet the matching criteria, typically selecting one control per case. Once eligible participants are identified, the GP practice will send a text message (drafted by the CLOCS-2 team).

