### Data sources and variables

#### Loyalty card data (for cases and controls)

CLOCS-2 participants or someone in their household will hold a loyalty card at one or both participating retailers that can be accessed by the UK population within all precincts, allowing the study to assess purchases of over-the-counter medications (ie, painkillers and indigestion medications) and eating habits. Eating habits will be used to identify dietary risk factors for specific cancers and to examine changes in dietary behaviour in response to potential cancer symptoms. The study will not include prescription-based pharmacy data which are not recorded in loyalty cards. After participants have provided consent, the CLOCS-2 team or the participant through the retailers’ OpenID platform (an interoperable authentication protocol that simplifies the way to verify the identity of users) will request their loyalty card data from the retailer, which will include individuals’ past purchase records from up to 6 years prior to the relevant cut-off date (study consent for controls or date of cancer diagnosis for cases). The purchase data will include each individual purchase, date of purchase, the location (ie, store postcode) and the product categorisation that is provided by the retailers. No additional individual information will be requested from the retailers.

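### The monthly Fisher's exact tests on pooled purchases treat items from the same shopper as independent, ignore the matched pairs and have no defined control count, so their p-values are miscalibrated

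*Protocol article*

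**What the plan says.** In the protocol article, Statistical methods names the test, the categories and the time grid. It plans Fisher's "exact tests comparing target (items suspected to be used to treat cancer symptoms) and non-target (all other items) purchases", and adds: "These comparisons will be made between cases and controls at each month prior to diagnosis". It then sets the comparator: "For controls, the reference will be the average monthly proportions of purchases across the observation period".

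Two other sections show what enters such a table:

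- Loyalty card data (for cases and controls) describes the records: "The purchase data will include each individual purchase, date of purchase, the location (ie, store postcode) and the product categorisation". One participant therefore supplies many rows, over up to 6 years.
- GP practices describes the matching: "GP practices will match invited cases with eligible controls based on age bracket, sex and the number of inhabitants", "typically selecting one control per case".

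The question of when cases and controls start to differ is given, in an earlier paragraph of Statistical methods, to a "multivariable, conditional logistic regression model with cancer as the outcome", with each participant's purchase proportion at different times as the exposure. Sample size and statistical power refers to the previous study, "conducted using conditional logistic regression of matched pairs", and states its requirement in pairs.

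The Fisher tests are given no adjustment for repeated items per person or for pairing. Autocorrelation is mentioned only for additional methods to be investigated.

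**The concern.** Both categories in the test are kinds of purchase, so the count in each cell is a number of items. Fisher's exact test takes those items to be independent. They are not: some households habitually buy more painkillers than others. The article's own section on bias lists reasons for this, namely uneven card use, buying for other household members, and buying for comorbidities. Heavy shoppers also carry more weight than light ones.

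There are two further faults. The test breaks the matched sets on which the design rests. And an average monthly proportion has no numerator and denominator of its own, so an analyst must invent a control count before the test can be run. The p-value depends on that choice.

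At stake are the months declared different. The primary objective is to find the time points at which purchasing differs significantly. A monthly series of p-values would be read as an answer to it, whether or not it agrees with the regression.

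**Working it through.** **Figures in the plan.** No figure is given for the Fisher tests. The 223 pairs belong to the matched analysis: 223/0.9 = 248, consistent with the target of 250 per cancer. Taking 10% off 250 leaves 225 per group, the size used here. Six years is up to T = 72 monthly tests.

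**Assumed inputs (not in the documents).** Mean items per person-month m, within-person correlation ρ (ICC), and a target share of 3%. The formulas take equal baskets and a buying tendency that is stable over the months. The simulations let baskets vary.

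**Comparison with same-month controls.** The true variance exceeds the assumed variance by the design effect D = 1 + (m − 1)ρ. The error rate at nominal 5% is 2[1 − Φ(1.96/√D)]. For m = 40:

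| ρ | D | Formula | Simulation, unequal baskets |
|---|---|---|---|
| 0.01 | 1 + 39×0.01 = 1.39 | 9.6% | about 10% |
| 0.02 | 1.78 | 14% | about 16% |
| 0.05 | 2.95 | 25% | about 32% |

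**Comparison as planned, with the control average entered as one month's counts.** In units of p(1 − p)/(Nm), the case month has variance 1 + (m − 1)ρ. The control average has (1 − ρ)/T + mρ: averaging over months removes most of the item noise but none of the between-person variation. The test assumes 1 + 1 = 2. The ratio of true to assumed variance is

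R = [1 + (m − 1)ρ + (1 − ρ)/T + mρ]/2,

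and the error rate is 2[1 − Φ(1.96/√R)].

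| m | ρ | R | Formula | Simulation |
|---|---|---|---|---|
| any | 0 | (1 + 1/72)/2 = 0.507 | 0.6% | 0.5% (run at m = 40) |
| 5 | 0.01 | (1.04 + 0.014 + 0.05)/2 = 0.552 | 0.8% | about 1% |
| 5 | 0.05 | (1.20 + 0.013 + 0.25)/2 = 0.732 | 2.2% | up to about 3% |
| 40 | 0.01 | (1.39 + 0.014 + 0.40)/2 = 0.902 | 3.9% | about 4% |
| 40 | 0.02 | (1.78 + 0.014 + 0.80)/2 = 1.297 | 8.5% | about 12% |
| 40 | 0.05 | (2.95 + 0.013 + 2.00)/2 = 2.482 | 21% | 20–30% |

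The simulated values at m = 40 are rough. In a run of 60 data sets, Monte Carlo standard errors are about 0.013, 0.027 and 0.044 for the three ICCs, because the 72 tests within a data set share the same people.

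The direction changes where R = 1, that is ρ = (1 − 1/72)/(2m − 1 − 1/72). This is 0.986/78.99 = 0.012 for m = 40 and 0.986/8.99 = 0.11 for m = 5.

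**Effect of the undefined control count.** Suppose all 72 months of control items were entered instead. The assumed variance becomes 1 + 1/72 = 1.014. At m = 40 and ρ = 0.01 the ratio is 1.804/1.014 = 1.78, and the error rate is 14% rather than 3.9%. The same sentence in the plan thus allows two quite different tests.

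**Effect of ignoring the pairs.** This acts in the opposite direction. With 223 pairs, a Fisher test on participants (bought any target item, 30% assumed) has error 4.0%, 3.1% and 1.5% at within-pair correlation 0, 0.1 and 0.3. At item level clustering still dominated in the one setting tried (m = 20, ρ = 0.05, same-month controls): 22% without shared rates and 19% when 30% of pairs shared the same rate.

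**A matched analysis by participant.** A paired comparison of participants' monthly proportions, on simulated data with m = 5 to 50 and ICC 0 to 0.10, stayed at 4.2–5.6%.

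**Expected false months.** If there is no true difference, 72 tests at 5% give 72×0.05 = 3.6 on average. At 12% they give 8.6, and at 0.5% they give 0.4.

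**The case against.** The strongest reply is that the timing question belongs to the conditional logistic regression, which keeps the pairs and uses one exposure value per person. The Fisher tests come later, with no stated role in fixing the divergence time. This stands: a reader might infer that the primary timing analysis is invalid, and the text does not support that.

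A second reply is that the p-values need not be too small. This also stands. A reader might infer from the same-month figures of about 10%, 16% and 32% that the plan will produce a surplus of false months. Those figures do not use the planned control reference. With that reference and small baskets the test is conservative, and ignored positive pair correlation pushes the same way. Basket size and ICC are not in the documents.

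A third reply is that the participant may be the intended unit. The wording does not say so. If it were, the clustering fault would fall away, but the pairs would still be ignored.

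Finally, an article may leave detail to an analysis plan. Here, though, the test, the categories and the comparator are stated. Further detail cannot make Fisher's test valid on pooled items; the unit or the test has to change.

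**Conclusion.** The point holds, confined to the Fisher tests. As written they count items as independent, ignore the matching and lack a defined control count. Their nominal 5% level is therefore unreliable in either direction: from under 1% without clustering to about 20–30% at 40 items a month and ICC 0.05, with the control average entered as one month's counts. These sizes rest on assumed basket size, ICC, target share and stable buying habits. Miscalibration follows from the stated rule, but its direction and size cannot be read from the documents.

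The regression used to define the divergence time is not affected. The practical risk is narrower: the Fisher tests address the same month-by-month question, are not labelled descriptive, and could give months that conflict with the regression. This should be fixed, but it does not undermine the main model.

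**What to change.** Drop Fisher's test on pooled items. For each month, summarise each participant once, as a target proportion or as any target purchase, and test within matched sets. Either of these will do:

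- a permutation test that swaps case and control labels within each pair, or
- the conditional logistic model already planned.

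A model of item counts clustered on participant and matched set is an alternative. If the item proportions are wanted for display, report them descriptively without p-values. Whichever route is taken, state how the control reference is formed from participants' data, and that the regression alone determines the divergence time.

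The cost is a change of wording and standard R code, with slightly more analysis work and no change to data collection. The p-values will be less favourable where clustering is material. Recruitment is planned to run until January 2028, so there is time to settle this before the final analysis.
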